## Abstract

**Background:**

During pregnancy, a sedentary lifestyle may have negative consequences on maternal and foetal health status. The main objective of this project is to assess the effects of an exercise intervention in overweight and grade I obese pregnant on maternal and foetal health markers.

**Methods/design:**

The present study aims to recruit 60 overweight and grade I obese women interested in participating in an exercise intervention program from the 17th gestational week until delivery. Women will be randomized to either an exercise (three 60-min sessions/week of combined aerobic and strength training and pelvic floor exercises), or usual care (control) group (30 women per group). The primary outcome measures are maternal weight gain, and maternal and neonatal glycaemic profile. Secondary outcome measures are: i) perinatal obstetric records; i) body composition; iii) dietary patterns; iv) physical fitness; v) low-back pain; vi) objectively measured physical activity and sedentary behaviour; vii) haematology and biochemical analyses; viii) oxidative stress; ix) pro- and anti-inflammatory markers; x) bone health biomarkers; xi) sleep quality; xii) mental health, quality of life and positive health.

**Discussion:**

The findings of this project will help to identify strategies for primary prevention and health promotion based on this exercise-based intervention program among overweight and grade I obese pregnant women.

**Trial registration:**

NCT02582567; Date of registration: 20/10/2015

## Background

Assessing the influence of lifestyle during pregnancy on maternal and foetal health is increasingly becoming a matter of interest [1–3]. Among these behaviours, physical activity (PA) may play an important role [4–8]. The sedentary lifestyle adopted by many pregnant women predisposes them to obesity, hypertension or gestational diabetes mellitus (GDM) [5, 6, 8], and the physiological changes occurring during gestation magnify this risk [9]. Importantly, overweight or obesity during pregnancy is associated with a significantly higher risk of pre-term delivery [10], birth-asphyxia-related complications [11], pre-eclampsia, GDM, prolonged labour, caesarean section, wound infection, postpartum haemorrhage, early neonatal death or neonatal intensive care admission [12–15], and infant mortality [16].

Maternal levels of PA may decline during pregnancy likely as a result of the physical changes of pregnancy and due to a combination of social and psychological factors, such as the thinking that resting during pregnancy is the safest behaviour [17, 18]. However, increasing PA levels during pregnancy is effective in the prevention of GDM, hypertension, dysnea, excessive gestational weight gain, and high birth weight, among others [5, 7, 8, 19, 20]. Emerging evidence suggest that exercise training during pregnancy (including moderate-to-high intensity exercise) might provide beneficial effects on both maternal and foetal health without side effects [21, 22]. Indeed, it has been shown that exercise during gestation prevents diastasis recti abdominis [23] and that higher levels of strength or aerobic training are positively associated with hospital stay length, incidence of cesareans and Apgar test [24]. Further, strength training may reduce the need for insulin in overweight pregnant with GDM [25]. Finally, aerobic and strength exercise improve physical fitness and result in additional benefits [26, 27]. Moreover, during pregnancy, not only the DNA of a new life is created, also programmed through epigenetics. In this sense, maternal exercise may have benefits on the newborn, such as higher neurodevelopment [28, 29], better heart functioning, improved heart rate variability [30] and less body fat [28]. However, it is unknown the extent to which supervised exercise programs might improve inflammatory markers, antioxidant activity or bone biomarkers. Moreover, most of exercise programs conducted in pregnant women are performed at light-to-moderate exercise intensity, or are based on solely aerobic or strength training.

An optimal mental health during pregnancy is also a major concern. High levels of depression or anxiety during gestation and post-partum affect maternal quality of life, and in turn, could have a negative influence on the foetal and child health [31, 32]. Exercise may improve the pregnant quality of life and reduce stress [33–36], which might protect the foetus [31]. Also, adequate sleep during gestation improves quality of life [37], prevents stress and depression [38–40] and GDM [41, 42], reduces inflammatory signal [43] and the incidence of preeclampsia, premature birth or caesarea [44–46]. Further, optimal sleep in pregnancy is essential for the foetal development [47] and a better mother-child relationship [40]. However, pregnancy frequently affects sleep quality [48, 49] and it would of clinical relevance to better understand whether an exercise program positively influences the pregnant sleep quality.

Therefore, the main objective of the GESTAtion and FITness (GESTAFIT) project randomized controlled trial (RCT) is to assess the effects of a novel supervised exercise intervention developed in overweight and grade I obese pregnant on maternal and foetal health.

The present methodological article describes the study design, procedures and methods that will be conducted in the “GESTAFIT project”.

## Methods/design

### Study design

A supervised RCT (registration number: NCT02582567) based on an exercise program will be conducted in 60 overweight (body mass index (BMI) ≥ 25–29.9), or grade I obese (BMI ≥ 30–34.9) pregnant women (*n* = 30 in the exercise intervention group vs. 30 controls) from Granada (southeaster Spain). The organizational and participants flow is presented in Fig. 1.

**Fig. 1 Fig1:**
[figure not shown]
Organizational and participants flow

The inclusion and exclusion criteria are described in Table 1. Participants will have to provide a written informed consent before taking part in the study, which will be conducted in accordance with the CONSORT (Consolidated Standards of Reporting Trials) statement [50]. Moreover, women will have to answer “No” to all questions from the PARmed-X for pregnancy health checklist (Physical Activity Readiness Medical Examination) by the Canadian Society for Exercise Physiology [51].

**Table 1 Tab1:** Inclusion and exclusion criteria in the GESTAFIT project

Inclusion criteria	
- Overweight or grade I obese pregnant woman aged 25–40 years old with a normal pregnancy course.	
- Answer “no” to all questions on the PARmed-X for pregnancy*.	
- To be able to walk without assistance.	
- To be able to read and write enough.	
- Informed consent: To be capable and willing to provide consent.	
*In addition, specific inclusion criteria for data analysis are: gestational age at delivery of 37–42 weeks with single foetus, spontaneous vaginal delivery or instrumental vaginal and caesarean without maternofoetal pathology (or other indication that does not involve maternofoetal risk, such as disproportion, failed induction, no foetal progression or non-cephalic presentation), newborn with appropriate weight, Apgar score > 7 in the 1st and 5th minute of life, cord blood pH (normal > 7.20) and normal monitoring results.	
Exclusion criteria	
- Acute or terminal illness.	
- Malnutrition.	
- Inability to conduct tests for assessing physical fitness or exercise during pregnancy.	
- Underweight, normal-weight or grade II-III obesity.	
- Pregnancy risk factors (such as hypertension, type 2 diabetes, etc.).	
- Multiple pregnancies.	
- Chromosopathy or foetal malformations.	
- Uterine growth restriction.	
- Foetal death.	
- Upper or lower extremity fracture in the past 3 months.	
- Presence of neuromuscular disease or drugs affecting neuromuscular function	
- Be registered in other exercise program	
- Perform more than 300 min of at least moderate physical activity per week	
- Unwillingness to either complete the study requirements or to be randomised into control or intervention group.	

PARmed-X for pregnancy: Physical Activity Readiness Medical Examination

This study was approved by the Clinical Research Ethics Committee of Granada, Government of Andalusia, Spain (code: GESFIT-0448-N-15). The study will be conducted following the ethical guidelines of the Declaration of Helsinki, last modified in 2013.

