## Randomization and blinding

After all the baseline evaluations, participants will be randomized to either the exercise intervention or the control group. A computer generated simple randomization sequence will be created before participants will be enrolled, to allocate participants to either group (1:1). The randomization sequence will be prepared by a member of the research team with no clinical involvement in the trial. The allocation will be concealed in a password protected computer file. Whereas the participants will be aware of their group allocation, outcome assessors and data analysts will be blinded to the allocation.

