## Exercise intervention

Most of exercise programs developed for pregnant women until now [20, 27, 52] have been designed in compliance with the recommendations of the American College of Obstetrics and Gynaecology (ACOG) in 2002 [53], or the Canadian Society for Exercise Physiology, among others [54]. However, in 2011, Zavorsky & Longo [55] launched a more actual, specific, and evidence-based guideline for exercise programs during pregnancy. Consequently, the exercise program that will be conducted in the present project has been developed accordingly to this guideline [55]. Nonetheless, we have also followed similar studies [56, 57] where aerobic and resistance training, as well as strengthening of the pelvic floor muscles [58], have been developed successfully and in line with these recommendations [57].

The exercise intervention (*n* = 30) will be performed in three groups of 10 participants and will meet the training standards of the American College of Sports Medicine [59] for adults. The groups will train 3 days/week (55–60 minutes per session) from the 17th week of gestation until delivery. The exercise sessions will be designed, carefully supervised, guided and instructed by qualified exercise professionals with experience in working with pregnant women.

The exercise program planning is shown in Table 3. The exercise intervention group will have different phases: a) *Information phase*: which will involve the understanding of the intervention plan for them, the goals we want to work with them, and how we will perform it (one training session); b) *Movement Learning phase*: theoretical and practical sessions with the explanation of movements and explanation of basic movement patterns (two training sessions); and c) *Physical Fitness Training phase*: with training sessions aimed at improving fitness and weight management (from the 18th until the 34th gestational week), and training sessions focused on a correct pelvic mobilization for the delivery (after the 34th gestational week until delivery) in order to try to reduce caesarean section rate, delivery time and number of pushes [23, 60].

**Table 3 Tab3:** Supervised exercise intervention program

SESION STRUCTURE	CONTENT										
WARM-UP 10 min	Joint mobility and different walk modalities										
CONDITIONING 40 min	Training week	1	2–4	5–6	7–8	9–10	11–12	13–14	15–16	17–18	>19
	Gestational week	17	18–20	21–22	23–24	25–26	27–28	29–30	31–32	33–34	>34

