### Secondary outcomes

#### Maternal and foetal outcomes

Birth weight; gestational age; type of delivery (natural, instrumental, or caesarean); Apgar scores (at 1 and 5 min); time of dilation, expulsion, and childbirth; GDM; and hypertension, will be obtained from perinatal obstetric records.

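### Table 1 limits the analysed women by birth results that arise after randomisation, and several of these are secondary outcomes

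*Protocol article*

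**What the plan says.** Table 1 (Methods/design, Study design) adds a second layer to the eligibility list: "specific inclusion criteria for data analysis are: gestational age at delivery of 37–42 weeks with single foetus". The same note requires "spontaneous vaginal delivery or instrumental vaginal and caesarean without maternofoetal pathology" (caesareans for certain other non-risk indications also qualify), then "newborn with appropriate weight, Apgar score > 7 in the 1st and 5th minute of life", and "cord blood pH (normal > 7.20) and normal monitoring results". It does not confine these conditions to any outcome.

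On timing, Randomization and blinding says: "After all the baseline evaluations, participants will be randomized to either the exercise intervention or the control group". Baseline is at week 16, and exercise runs from week 17 to delivery.

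Secondary outcomes (Maternal and foetal outcomes) begins with "Birth weight; gestational age; type of delivery (natural, instrumental, or caesarean" and goes on to Apgar scores. The Foetus/newborn section classifies babies as low birth weight (below 2500 g) or macrosomic (above 4000 g). The Exercise intervention section says the late sessions are designed "in order to try to reduce caesarean section rate, delivery time and number of pushes", and cites an earlier study of this training type as showing less preterm birth and more vaginal delivery.

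Statistical analysis defines a per-protocol set by at least 80% attendance and completed baseline and follow-up evaluations. It adds intention-to-treat and baseline-carried-forward sensitivity analyses. It neither repeats nor lifts the Table 1 conditions.

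**The concern.** A condition that is known only at birth cannot be an entry criterion. Used to choose who is analysed, it selects on events that follow allocation and that treatment may change.

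Two things are at stake. First, outcomes that are also filter conditions are truncated: benefit and harm on them disappear together, including a harm such as preterm birth. Second, the remaining outcomes are compared between groups that may have passed the filter at different rates and for different reasons, so randomisation no longer guarantees comparability. That reaches the primary outcomes. The cord glucose/insulin ratio would be seen only among good births, and women could be dropped from the weight-gain and HOMA-IR analyses because of events after the week-34 measurement.

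**Working it through.** **1. The plan's own figure.** Inputs from Sample size: difference 1.04 kg, SD 1.15 kg, power 90%, α 0.05 (two-sided taken). n per group = 2(1.960 + 1.282)² × 1.15² / 1.04² = 25.7, so 26 per group and 52 in total, as stated. After 15% loss, 30 × 0.85 = 25.5 per group remain, with power about 0.90. The sample size is not in dispute. Its only allowance is for loss to follow-up.

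**2. Timing and overlap.** Delivery at 37–42 weeks falls 37 − 16 = 21 to 42 − 16 = 26 weeks after baseline.

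| Condition for analysis | Settled after randomisation? | Also a listed outcome? |
|---|---|---|
| Delivery at 37–42 weeks | Yes | Yes (gestational age) |
| No caesarean for maternofoetal pathology | Yes | Partly (type of delivery) |
| Appropriate newborn weight | Yes | Yes (birth weight, low birth weight, macrosomia) |
| Apgar > 7 at 1 and 5 min | Yes | Yes |
| Cord pH > 7.20, normal monitoring | Yes | No |
| Single foetus | No (multiple pregnancy already excluded) | No |

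For gestational age, newborn weight and Apgar, the excluded events have frequency 0 in both filtered arms by construction.

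**3. Truncation of birth weight (illustration; all inputs assumed).** Table 1 does not define appropriate weight, so I borrow 2500–4000 g from the Foetus/newborn section. Take a true effect of −150 g. The truncated mean is μ + σ[φ(A) − φ(B)]/[Φ(B) − Φ(A)], with A = (2500 − μ)/σ and B = (4000 − μ)/σ.

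| Control mean (g) | SD (g) | Difference after filter (g) | Shrinkage |
|---|---|---|---|
| 3450 | 400 | 105.9 | 29% |
| 3450 | 480 | 85.8 | 43% |
| 3450 | 550 | 71.2 | 53% |
| 3300 | 400 | 108.4 | 28% |
| 3300 | 550 | 72.0 | 52% |

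At 3450 g and SD 480, macrosomia of 12.6% against 7.2% becomes 0 against 0.

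**4. Retention and power (pass rates assumed).** For five independent filters:
- 0.95 × 0.92 × 0.95 × 0.90 × 0.95 = 0.71
- 0.90 × 0.85 × 0.90 × 0.80 × 0.90 = 0.50

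If failures overlap fully, the lowest single rate governs, so 0.90 and 0.80 are retained. If the filter removes 10, 20, 30 or 40% of completers, 25.5 per group falls to about 23.0, 20.4, 17.9 or 15.3. Power for weight gain falls to 0.865, 0.823, 0.771 or 0.706.

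**5. Selection effect on weight gain (assumed model).** Suppose exercise has no true effect on weight gain, and weight gain correlates ρ with a latent birth-risk factor that decides who is filtered out. With λ(p) = φ(z₁₋ₚ)/(1 − p), the spurious difference (exercise minus control) is 1.15 × ρ × [λ(p control) − λ(p exercise)].
- ρ = 0.2, 30% against 20% removed: 1.15 × 0.2 × (0.497 − 0.350) = 0.03 kg
- ρ = 0.5, 40% against 20% removed: 1.15 × 0.5 × (0.644 − 0.350) = 0.17 kg
- equal removal rates: 0

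This is 3–16% of the 1.04 kg target, and exercise would appear to gain more. The documents give nothing from which to size the effect on the cord ratio.

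**The case against.** The strongest reply is that the Statistical analysis section governs. It defines the analysed set without the birth conditions and promises an intention-to-treat analysis, which ordinarily means all randomised women. Classifying low birth weight and macrosomia would also be pointless if those babies were always removed, so the note may have been meant mainly for cord-blood material.

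Part of this stands: one cannot be certain that adverse births would be missing from every analysis. But Table 1 sets no such limit, intention-to-treat is only a sensitivity analysis, and nothing says the filter is lifted for it. The protocol contradicts itself, and the reading that follows Table 1 is the damaging one.

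A reader might infer more than the text supports:
- **That every condition is a trial outcome.** Cord pH and monitoring are not listed as outcomes, and single foetus is fixed before randomisation.
- **That gestational diabetes and hypertension are filtered out.** The note names neither.
- **That the caesarean comparison is erased.** Vaginal and instrumental deliveries stay in, as do caesareans for disproportion, failed induction, lack of progress or non-cephalic presentation.
- **That the weight-gain result would be badly distorted.** The assumed model gives little bias, and none when both arms are filtered equally.

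**Conclusion.** The point holds and should be settled before any analysis. As written, Table 1 conditions the analysis on post-randomisation events and conflicts with the listing of gestational age, birth weight and Apgar as outcomes. Type of delivery is affected in part. The disappearance of preterm birth, inappropriate birth weight and low Apgar from both arms follows from the rule itself and needs no assumption.

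Selection is also built into the cord glucose/insulin comparison, at a size the documents do not allow one to estimate. For week-34 weight gain and HOMA-IR the effect is probably smaller; the illustration covers weight gain only. The 28–53% shrinkage, the retention of 50–71% (independent filters) or 80–90% (full overlap), and the power losses all rest on assumed inputs and show plausible scale only. The 15% loss allowance does not cover the filter.

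**What to change.** Remove the birth-outcome conditions from Table 1 as a filter for all outcomes, and keep as eligibility criteria only what is fixed before randomisation, such as singleton pregnancy.

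Deleting the note is not enough, because the per-protocol rule would still define the main set. Add to Statistical analysis that the analysis sets include randomised women with outcome data regardless of how the birth went. At minimum this must cover the intention-to-treat analysis and all perinatal outcomes.

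The uncomplicated-term-birth subset may remain as a labelled supplementary analysis of cord-blood biomarkers, with appropriate weight defined.

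The cost is wording in two sections; the perinatal records are already to be collected. The downside is somewhat more heterogeneous cord-blood data.

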## Recruitment process and measurements procedures

The evaluation protocol scheme is shown in Table 2. The measurements will be carried out in different days. The first assessment day will coincide with the 12th gestational week visit to the gynaecologist at “San Cecilio” University Hospital, Granada, and potential participants will be individually informed about the study objectives, evaluation protocol and procedures. If the woman agrees to participate in the present RCT, the researcher will provide detailed information about each of the phases of the study, and the participant will be asked to read and sign written informed consent. Subsequently (on the same day), weight and height will be assessed. On the second assessment day (16th gestational week) participants will attend the research centre and they will complete the following assessments: nutritional and clinical information, blood pressure, resting heart rate and physical fitness. The initial survey (anamnesis) will be conducted through face-to-face interviews by trained staff in order to gather data on sociodemographic characteristics, reproductive history, history of illness (hypertension, diabetes, obesity, etc.), and diet. Other health information will be collected using a self-administered questionnaire and it will include personal questions regarding smoking and alcohol habits and indicators of socio-demographic and socio-economic status (such as personal and household income, educational level or marital status). This survey will also include questions regarding the employment of nutritional supplements or special diets. Participant will then receive the accelerometer and questionnaires to be completed there or at home, and will be asked to return them eight days later. Additionally, the Hospital will make an appointment with the participants during that week for the biochemical and urine samples collection. The third day of evaluation will consist on accelerometry and sleep quality assessment on the 24th week of gestation. The fourth day of evaluation will take place on the 34th week of gestation. This evaluation will be exactly the same to that performed in the second day of evaluation before the exercise program started (i.e. 16th gestational week), including biochemical assessments.

**Table 2 Tab2:** Evaluation protocol scheme

	Criteria (12th week)	Baseline (16th week)	Second trimester (24th week)	Third trimester (34th week)	Delivery	1 month post-partum
Informed consent	X					
1st day evaluation						
Sociodemographic data		X				
Clinical history		X		X	X	X
Weight and height	X	X		X		X
Body composition (dual-energy x-ray absorptiometry)						X
Accelerometry		X	X	X		
Physical fitness		X		X		
Nutritional study		X		X		X
Questionnaires to be fill there or at home between the 1st and 2nd evaluation days						
Low back-pain		X		X		X
Quality of life		X		X		X
Sleep quality		X	X	X		X
Physical activity		X	X	X		X
Self-perceived physical fitness		X	X	X		X
Sexual function		X		X		X
Restless legs syndrome		X		X		X
Mental and positive health		X		X		X
2nd day evaluation: Accelerometers collection and review of questionnaires		X		X		
Maternal biochemical analysis		X		X	X	
Umbilical cord blood sampling					X	
Maternal urine sampling		X		X	X	

Blood samples (5 mL) of all pregnant participants will be extracted at week 16th and 34th of gestation, and at delivery. Samples of venous and arterial blood from the umbilical cord (5 + 5 mL) at the time of delivery will be taken. In addition, samples of urine at 16 and 34 weeks gestation and delivery will be collected. All samples will be immediately frozen and conserved at −80 °C to avoid breaking the cold chain before being sent to the laboratory.

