## Primary and secondary outcomes

### Primary outcome

The primary outcomes are maternal weight gain and maternal and foetal glycaemic profile. Maternal weight gain will be defined as the weight change from baseline measurement to the last measurement at 34th week of gestation. Maternal insulin sensitivity will be derived from the homeostatic model assessment for insulin resistance (HOMA-IR), which will be calculated using the formula [fasting insulin (μIU/mL) × fasting glucose (mg/dL)]/405 in the 34th week of gestation. Neonatal insulin sensitivity will be assessed through the cord blood ratio glucose/insulin.

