#### Maternal and foetal anthropometry and body composition

##### Maternal

Height will be measured only at the baseline measurement with a stadiometer (Seca 22, Hamburg). Pre-pregnancy weight will be based on self-report. Height measurement and pre-pregnancy weight will be used to calculate BMI (weight[Kg]/height[m2]) [65].

One month after delivery (postpartum period) lean, fat and bone mass of the whole body will be measured using a dual-energy x-ray absorptiometry (DXA) device (Hologic Discovery QDR, Nasdaq: HOLX). Waist circumference (cm) will be assessed at the middle point between the ribs and the ileac crest, with the participant standing (Harpenden anthropometric tape, Holtain Ltd).

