## Statistical analysis

Since this study aims at determining potential biological effects of exercise, the statistical analysis will be performed on a per-protocol basis, thus, including in the analyses only participants who attended at least 80 % the exercise session and completed both baseline and follow-up evaluations. The treatment effects will be reported as between-group changes on the primary and secondary outcomes and will be assessed with generalized linear models after adjusting for baseline values. All the analyses will be repeated additionally adjusting for age and any other confounder potentially not well balanced at baseline, and the results from both models will be reported. The effect size (95 % confidence interval) and statistical significance will be reported for each study outcome. The statistical significance will be set at α = 0.05. Sensitivity analyses will be conducted using intention-to-treat analyses and baseline observation carried forward imputation.

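### The primary weight-gain outcome has no pregnancy weight between randomisation and week 34, despite a week-24 evaluation, and no model names the week-12 weight; the benefit of changing this is small but the change is cheap

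*Protocol article*

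**What the plan says.** - **Outcome.** Primary outcome section: "Maternal weight gain will be defined as the weight change from baseline measurement to the last measurement at 34th week of gestation".
- **Weighing schedule.** The Table 2 row reads "Weight and height X X X X". The four marks fall at week 12, week 16, week 34 and one month post-partum. Week 24 and delivery are blank.
- **Week 24.** Recruitment process and measurements procedures: "The third day of evaluation will consist on accelerometry and sleep quality assessment on the 24th week of gestation". Table 2 adds the physical activity and self-perceived fitness questionnaires at that visit.
- **Week 12.** Same section, at the consent visit before randomisation: "Subsequently (on the same day), weight and height will be assessed".
- **Which visit is baseline.** Table 2 heads the week-16 column "Baseline (16th week". However, the text list for week 16 is "nutritional and clinical information, blood pressure, resting heart rate and physical fitness", which omits weight. The Maternal anthropometry section says "Height will be measured only at the baseline measurement with a stadiometer", although the text measures height at week 12.
- **Model.** Statistical analysis section: treatment effects "will be assessed with generalized linear models after adjusting for baseline values". A second model adds age and any confounder that looks unbalanced.
- **Analysis set.** The main analysis keeps women with at least 80% attendance and both evaluations complete. Intention-to-treat with baseline observation carried forward is a sensitivity analysis.

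**The concern.** The outcome that sizes the trial has a single post-randomisation measurement during pregnancy, about 17 weeks after the exercise programme starts (week 17 to week 34). Accelerometry, sleep and two other questionnaires get an interim reading at week 24, but weight does not.

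This matters for women who are lost. The main analysis excludes them. The sensitivity analysis that should include them has no interim pregnancy weight to work with, and instead assigns each of them no gain from baseline to week 34. The one-month post-partum weight is no substitute, because it is taken after delivery and does not measure gestational gain. A later analysis plan can change the model, but it cannot recover a weight that was never taken.

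Separately, every woman has two weights before randomisation. Together they carry her own rate of gain from week 12 to week 16, which might predict later gain. No stated model names the second weight.

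**Working it through.** **1. The plan's own figure.** Sample size section: difference 1.04 kg, SD 1.15 kg, power 90%, α 0.05 (two-sided reproduces).

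n per arm = 2 × (1.960 + 1.282)² × 1.15² / 1.04² = 25.7, so 26 per arm and 52 in total, as stated. Normal-approximation power is 90.3%; the t-test gives 89.2%. The sample size is not in question.

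**2. Women without a week-34 weight.** 60 × 0.15 = 9. If losses are spread evenly over weeks 17 to 34 (assumption), 10 of those 18 weeks come after week 24, so 9 × 10/18 = 5 of the 9 could have been weighed at week 24.

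**3. What baseline carried forward does.** The documents give no mean gain, so assume 6 to 10 kg from week 16 to week 34, and 15% loss in each arm unrelated to gain. The expected difference becomes 0.85 × 1.04 = 0.88 kg. The SD becomes √(0.85 × 1.15² + 0.15 × 0.85 × g²).

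| Assumed gain g | SD | Power, 30 per arm |
|---|---|---|
| 6 kg | 2.39 | 29% |
| 8 kg | 3.05 | 20% |
| 10 kg | 3.72 | 15% |

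One extra lost woman in one arm of 30 lowers that arm's mean gain by g/30, that is 0.20 to 0.33 kg.

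**4. Week-24 weight, loss unrelated to gain.** In a likelihood model the variance of an arm mean is proportional to (1 − ρ²)/n₁ + ρ²/n₂. Here n₁ = 25.5 completers, n₂ is completers plus lost women weighed at week 24, and ρ is the correlation between gain to week 24 and gain to week 34 (not in the documents). With ρ = 0.7 and half the lost women weighed, n₂ = 27.75:

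0.51/25.5 + 0.49/27.75 = 0.0377, so effective n = 26.6 per arm against 25.5. The standard error ratio is √(25.5/26.56) = 0.98.

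For ρ from 0.3 to 0.9, with half or all of the lost women weighed, effective n is 25.7 to 29.0 and power rises from 89.8% to between 90.0% and 93.1%. A simulation of 30 + 30 women at ρ = 0.6/0.7/0.8 gave standard errors of 0.322/0.325/0.325 without the week-24 weight and 0.316/0.318/0.315 with it, a fall of 2 to 3%.

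**5. Week-24 weight, informative loss.** Assume that exercise-arm dropout rises with early gain (log-odds 1 per SD), control loss is random, and the true effect is −1.04 kg.

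| ρ | Completers | With week-24 weight | Bias removed |
|---|---|---|---|
| 0.6 | −1.119 | −1.067 | 0.05 kg |
| 0.7 | −1.133 | −1.071 | 0.06 kg |
| 0.8 | −1.149 | −1.080 | 0.07 kg |

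A separate large-sample run gave −1.14/−1.15/−1.16 and −1.08/−1.08/−1.09, so the same 0.05 to 0.07 kg. Against a standard error of 0.32 kg that is about one fifth of a standard error.

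**6. Second pre-randomisation weight as covariate.** The residual variance of week-34 weight was compared given week-16 weight alone and given weeks 12 and 16 together. Assumptions: between-woman SD 8 kg, early-gain SD 0.3 to 0.5 of the later-gain SD, weighing error 0.2 to 0.4 kg, correlation of early with later gain 0 to 0.5. With later-gain SD 1.15 kg, the variance falls by 0 to about 14%. At 14%, the t-test power at 26 per arm rises from 89.2% to 93.2%, and 52/0.86 = 60, equivalent to about 8 extra women. At the bottom of the range nothing is gained and one degree of freedom is spent.

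**The case against.** A change between two time points adjusted for baseline is a standard and valid design. Choosing an extra covariate or a repeated-measures model is often left to an analysis plan, which is not shown here. That is a fair reply on the covariate, and it is why this point is a suggestion rather than a correction. It does not answer the missing week-24 weighing, which is fixed by the schedule.

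Three stronger readings are tempting, and the documents do not support them:

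- **That every woman lost before week 34 has no post-randomisation weight.** A woman who misses only week 34 may still be weighed one month post-partum. What she lacks is an interim weight during pregnancy.
- **That nothing collected could correct bias from informative loss.** Weights at weeks 12 and 16 and the week-24 accelerometry and questionnaires could serve as auxiliary data. How well they predict gain is unknown.
- **That leaving out week 12 certainly discards precision.** The documents give no correlation, and the range starts at zero.

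Three further limits stand. Attendance in person at week 24 is implied by the wording but not stated: questionnaires may be completed at home, and the Table 2 row for accelerometer collection is marked at weeks 16 and 34 only. Treating week 12 as the unused weight relies on Table 2's label; if week 12 is the baseline, week 16 is the unused weight and the argument is the same. Finally, the completer-only main analysis would still exclude women lost after week 24, whatever is measured then.

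**Conclusion.** The point holds as a low-priority improvement. No pregnancy weight is scheduled between randomisation and week 34, one of the two pre-randomisation weights is not named in any model, and the text and Table 2 do not agree clearly on which visit is baseline. The practical consequence falls mainly on the intention-to-treat sensitivity analysis, where about 9 of 60 women would be assigned zero gain.

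The size is modest and rests on correlations and a dropout mechanism that the documents do not give. The bias figures need strong dropout on gain in one arm only; a variant in which women lost before week 24 leave at random gave a smaller completer bias, 0.06 to 0.08 kg. The low power shown for baseline carried forward should not be credited to the week-24 weight. That rule can be dropped without an interim weight, but lost women would then add almost nothing to the week-34 contrast.

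**What to change.** 1. **Baseline and covariates.** Reconcile the recruitment text, the Maternal anthropometry section and Table 2 on which visit is the baseline for weight. Prespecify both pre-randomisation weights (weeks 12 and 16) as covariates in the weight-gain model. With both in a linear model, the arm contrast is the same whichever visit is labelled baseline. Cost: a sentence or two of wording, no new data, one degree of freedom.
2. **Week-24 weight.** Provided women attend in person, mark weight at week 24 in Table 2 for both arms. Run the intention-to-treat weight analysis on all randomised women with a repeated-measures model of week-24 and week-34 weights (arm by visit, both pre-randomisation weights as covariates, week-34 contrast), in place of baseline carried forward. Cost: a brief weighing and a minor amendment. If there is no in-person visit at week 24, the cost is higher and the case correspondingly weaker.

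If the week-24 weight is also meant to inform the main result, the completer-only analysis set has to change as well.
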